### Data Analysis

Baseline demographics will be summarized as frequency (%) for categorical variables and as mean (SD) or median (interquartile range, IQR) for continuous variables, depending on the distribution. The number of compliant participants within each cohort will be summarized as frequency (%). The number (%) of patients who attained their step goal will be summarized weekly and by cohort, along with the median number of weeks where goals were attained.

The daily step count will be summarized at week 1 and week 10 for each cohort as mean (SD) or median (IQR). The mean difference between week 1 and week 10 will be displayed alongside the corresponding 95% CI. Data will be analyzed on the days the accelerometer was worn, defined as more than 250 steps.

Quality-of-life questionnaires will be summarized as median (IQR) or mean (SD) at the initial and week 10 visit for each cohort group. The mean difference between time points will be displayed alongside the 95% CI.

The frequency (proportion) of opened emails will be summarized for Cohort 2 and Cohort 3 by each week of the study, and the number of PMs opened by Cohort 3 will be summarized as frequency (%).

The number of symptoms reported will be used to investigate the association of baseline characteristics with engagement in the study. A Mann-Whitney *U* test will be used to compare the number of symptoms between categorical variables, and Spearman correlation will be used to investigate the association with continuous variables.

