**Methods:**

Using a longitudinal cohort design, people with cancer will be serially allocated to 3 intervention cohorts of 20 participants each and followed for 10 weeks. Cohort 1 will be provided a wearable activity monitor and access to a Web-based portal. Cohort 2 will receive the same content as Cohort 1 and in addition will receive a weekly activity summary message. Cohort 3 will receive the same content as Cohorts 1 and 2 and in addition will receive a personalized weekly coaching message. Feasibility of the use of the portal is the primary outcome.

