### Recruitment Procedure

There will be rolling serial recruitment into each of the 3 cohorts. Once 20 participants have been recruited for Cohort 1, recruitment will then start for Cohort 2. After 20 additional participants have been recruited for Cohort 2, recruitment will start for Cohort 3. Eligible patients will be identified by either a clinical nurse consultant, physical therapist, or a supportive care and integrative medicine specialist. The clinician will provide a written participant information sheet to potentially eligible participants. Potential participants consenting to be contacted will be screened to confirm eligibility and will be provided verbal information about the study. Participants will be registered into the study after signing the informed consent form during their individual orientation session. Due to the nature of working with a population who are undergoing intensive cancer treatment, a slight attrition is expected to occur in each cohort.

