#### Web Portal Access

Participants will have access to the Web portal for 8 weeks after the goal setting session, 10 weeks in total. During this time, data, both from the activity tracker and those which are manually entered, will be collected and will be accessible for both the participant and study investigators. Participants will be asked to wear the activity tracker for the duration of the study and synchronize their device daily. Participants will able to track their fatigue and pain scores daily on the Web portal. These symptoms will be rated on a Likert scale from 0 (none) to 10 (worst imaginable) using a drop-down menu.

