### Primary and Secondary Outcomes

The primary outcome of interest is the feasibility of the program. The intervention would be deemed feasible if a compliance rate of >70% is observed.

Compliance is defined based on 2 measures:

Log-ins: a patient is defined as compliant if they have more than 2 log-ins over the 10-week study period.Questionnaires: a patient is defined as compliant if they complete the follow-up questionnaire at week 10.

For the study to be deemed feasible, >70% of the participants need to comply with both criteria, not just one.

The secondary objectives of the study are as follows:

To describe goal attainment; the number of individuals who are eligible and take up the program; the rate of program completion; satisfaction with the intervention; self-efficacy related to change in lifestyle factors; and clinical changes including symptom and HRQoL scoresTo analyze Web portal data to determine median daily step count, weekly email engagement (Cohorts 2 and 3), and number of PMs sent (Cohort 3)To compare accelerometer data from the first week (week 1) and final week (week 10).

**Table 1 table1:** Data collection schedule. Checkmarks indicate time points when data were collected.

Data collection	Preregistration	Baseline	Week 2	During the intervention	Week 10
Eligibility check	✓				
Consent		✓			
Demographics		✓			
Goal setting			✓		
Functional Assessment of Cancer Therapy-General		✓			✓
Edmonton Symptom Assessment Scale		✓			✓
Cancer Behavior Inventory-Brief version		✓			✓
Pain score (0-10)			✓	✓	
Fatigue score (0-10)			✓	✓	
Activity tracker data			✓	✓	
Web portal usage data				✓	
Adverse events				✓	
Participant survey					✓
Interviews					✓

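### The week 1 to week 10 step change describes only participants still wearing and synchronizing the tracker in week 10, and is biased upward if stopping goes with falling activity

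*Protocol article*

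**What the plan says.** The Data Analysis section of the protocol article summarizes daily steps by cohort at weeks 1 and 10, and continues: "The mean difference between week 1 and week 10 will be displayed alongside the corresponding 95% CI". It then restricts the data: "Data will be analyzed on the days the accelerometer was worn, defined as more than 250 steps". The restriction applies to both weeks. The article does not say whether the difference is paired.

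Under Web Portal Access, the data depend on what participants do: "Participants will be asked to wear the activity tracker for the duration of the study and synchronize their device daily". Under Recruitment Procedure, the article points to intensive treatment and says that "a slight attrition is expected to occur in each cohort", without a percentage. The Introduction reports that people receiving chemotherapy or radiation usually become much less active.

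The comparison of weeks 1 and 10 is listed as a secondary objective under Primary and Secondary Outcomes. In the same section, "The primary outcome of interest is the feasibility of the program".

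**The concern.** A within-person change needs a qualifying day in both weeks. Someone who leaves the study, stops wearing the tracker or stops synchronizing before week 10 contributes nothing to it, however many earlier weeks were recorded. The estimate is therefore conditional on continued wear, and its CI carries no allowance for those who are absent.

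The article names the same cause, intensive treatment, for declining activity and for expected attrition. If people who stop are also those whose activity is falling, the remaining participants show a better mean change than the cohort that enrolled. The Discussion expects the results to inform the design of a randomized trial, so an inflated change could carry over into its planning. Loss that differs between cohorts would also blur any informal reading of the three changes side by side.

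Wear is also inferred from the outcome itself. A worn day with 250 steps or fewer is treated as non-wear, which could matter for the least active patients.

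**Working it through.** **Inputs from the article.** The design is "people with cancer will be serially allocated to 3 intervention cohorts of 20 participants each and followed for 10 weeks". The worn-day cut is 250 steps. Attrition is expected but not quantified. No SD, dropout rate or target change for steps is given, so there is no planned figure to reproduce. Every other input below is an assumption.

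**1. Selection bias.** Let *m* be the fraction with no week 10 value, *C* the mean change in those observed, and *d* the amount by which the mean change is worse in those missing.

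- Mean change in everyone = (1 − *m*)·*C* + *m*·(*C* − *d*) = *C* − *m*·*d*
- Bias of the observed mean = *C* − (*C* − *m*·*d*) = *m*·*d*

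| Missing at week 10 (*m*) | *d* = 0 | *d* = 500 | *d* = 1,000 | *d* = 2,000 |
|---|---|---|---|---|
| 10% (2 of 20) | 0 | 50 | 100 | 200 |
| 20% (4 of 20) | 0 | 100 | 200 | 400 |
| 30% (6 of 20) | 0 | 150 | 300 | 600 |

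All entries are steps/day. If the difference is instead taken between unpaired weekly means, *d* becomes the gap in week 10 level, which is the gap in change plus any gap already present in week 1. The problem is then no smaller in principle.

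**2. Simulation.** True mean change 0, SD of change 1,500, and a logistic probability of missing week 10 that rises as the change worsens (log-odds slope per SD of change: 0, −0.7 or −1.5).

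| Missing | Unrelated to change | Moderate relation | Strong relation | Decliners still included (moderate; strong) |
|---|---|---|---|---|
| 10% | +1 | +101 | +181 | 85%; 82% |
| 20% | −1 | +196 | +342 | 72%; 66% |
| 30% | +2 | +289 | +494 | 59%; 51% |

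Columns two to four give the observed mean change in steps/day. The values of −1 to +2 are simulation noise around zero.

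**3. The 250-step cut alone.** Daily steps were taken as lognormal with a coefficient of variation of 0.5 or 0.8.

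- Mean 2,000 steps/day: at most 0.5% of days removed.
- Mean 1,000: 0.3% to 5% removed.
- Mean 500: 11% to 26% removed, which raises the worn-day mean to between 535 and 617.
- Chance that all 7 days of a week are removed: below 0.0001 even at a mean of 500.

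So the cut by itself hardly ever removes a person who is wearing the device. The selection arises from stopping wear or synchronization.

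**4. Scale.** With 20 people and the assumed SD of 1,500, the 95% CI half-width is 2.093 × 1,500/√20 = 702 steps/day. The Goal Setting Session section sets goals typically 10% above baseline; on an assumed 5,000-step baseline that is 0.10 × 5,000 = 500 steps/day. A bias of 100 to 200 would be 100/500 = 20% to 200/500 = 40% of that goal increment.

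**The case against.** A reader might infer that the worn-day rule itself takes out people whose activity falls. The documents do not support that. Someone who drops from 5,000 to 2,000 steps and keeps wearing and synchronizing the device stays in, the cut matters only at very low activity, and it acts in week 1 as well as week 10. Excluding non-wear days is a sensible way to avoid counting an unworn device as near-zero activity.

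Nor is the direction of bias certain. A short spell of wear that passes 250 steps counts as a full day. If such partial days become more common by week 10, they pull the estimate down. Attrition is described only as slight, so the 30% rows fit the text poorly. At 10% to 20% missing and *d* = 1,000, the bias is well inside the assumed CI half-width for one cohort.

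The endpoint is secondary and descriptive, with no test or decision attached. Feasibility rests on log-ins and the week 10 questionnaire, not on steps. The plan does use the intervening weeks elsewhere, in its weekly summary of goal attainment. A minimum-wear rule and the handling of missing week 10 data may sit in a fuller document, so their absence is no fault here.

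All of this stands and limits the point. It does not change what the stated contrast estimates: a change among people with recorded worn days at both ends.

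**Conclusion.** The point holds in a limited form. As stated, the step change is an available-data estimate conditional on still wearing and synchronizing the tracker above 250 steps in week 10. An upward bias is plausible from the article's own account of treatment, activity and attrition, but the article does not establish it or allow its size to be calculated. Under an assumed 10% to 20% missing with a change 1,000 steps/day worse, it is about 100 to 200 steps/day; if missingness is unrelated to change, it is zero. The primary feasibility outcome is unaffected. This is a cheap improvement to a secondary estimate, and it does not show that the planned result would be wrong.

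**What to change.** - **Main estimate.** Obtain the week 10 minus week 1 change for each cohort from a linear mixed model on worn-day steps from all 10 weeks, with week-by-cohort fixed effects and participant random effects. Participants who stop early then contribute the weeks they have.
- **Secondary display.** Keep the simple difference, label it as applying to continuing wearers, and show the participants and worn days behind each week's value. Do not add a minimum number of worn days to this display, since that would remove more low-wear participants and sharpen the selection.
- **Sensitivity analysis.** Repeat with synchronized days of 250 steps or fewer included, as a lower bound. Some of those days will be true non-wear, so this is a bound and not a better estimate. Because it also lowers week 1, show both weekly levels as well as the change.

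**Cost.** The daily data are already collected, so this means one standard model, one table and one rerun. The Results section says that analysis is under way, so the change should be dated and reported as an addition. The model replaces restriction to continuing wearers with a missing-at-random assumption; it does not remove bias if missingness depends on unobserved week 10 activity.

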### Ethics

Permission to conduct this study has been granted by the Royal Prince Alfred Hospital Human Research and Ethics Committee (X16-0051). All participants will provide written informed consent, and the study will be conducted in accordance with the Declaration of Helsinki and applicable national guidelines.

## Results

The project was funded in 2016, and enrollment was completed at the end of 2017. Data analysis is currently under way, and the first results are expected to be submitted for publication in 2018.

## Discussion

Reduced physical activity levels during cancer treatment can lead to increased symptom burden and consequently reduced quality of life. There is no single solution to facilitate positive behavior change across a population of people with cancer in active treatment; however, the innovative use of technology may benefit a proportion of the population. Patients with cancer who have tertiary education, who are undergoing intensive treatment, and those who report reduced HRQoL express a more positive perception of and openness to use of Web portals [8,27]. Despite an overall positive perception of eHealth interventions, there are varying perceptions of their usability from both patients and clinicians, although benefits to self-management and outcomes have been demonstrated [8,9].

It is acknowledged that this study will recruit a heterogeneous patient sample, with various tumor types and treatment stages represented. However, the decision to include a heterogeneous sample was deemed appropriate for a feasibility study and is also pragmatic for recruiting the required sample within a short time frame as well as the generalizability of the findings. Where patient numbers are sufficient, we will explore the impact of the intervention on specific tumor groups, stages of disease, and point in the cancer treatment trajectory to inform the design of any future efficacy trials.

The utility of Web portals for clinicians and clinician-patient relationships is an important benefit of such systems. This study does not include data review or interactions with medical specialists; rather, it will be limited to an exercise professional. Depending on feasibility, future iterations will include such components.

Determining the feasibility of the intervention is the major objective of this study. The inclusion of qualitative interviews strengthens the study and will help to guide future development of the system and studies. User-designed health systems have been shown to increase functionality, specificity, and uptake [28].

Results from this prospective cohort study will add to the body of evidence surrounding the use of eHealth initiatives to facilitate physical activity behavior change and symptom tracking in people with cancer. It is anticipated that the results of this pilot will inform the design of a future randomized controlled trial that will be adequately powered to assess clinically relevant outcomes.

## Abbreviations

EP: exercise physiologist
HRQoL: health-related quality of life
IQR: interquartile range
PM: personalized message
PRO: patient-reported outcome
REDCap: Research Electronic Data Capture
SMS: short message service
